**Table 13 Severity grading criteria for temperature (adolescents aged 13 and above).**

|                |                                                                                                                                        |
|----------------|----------------------------------------------------------------------------------------------------------------------------------------|
| GRADE 0 | None                                                                                                                                   |
| GRADE 1 | Mild: Transient or mild discomfort (< 48 hours); No interference with activity; No medical intervention/therapy required               |
| GRADE 2 | Moderate: Mild to moderate limitation in activity – some assistance may be needed; no or minimal medical intervention/therapy required |

|                |                                                                                                                 |
|----------------|-----------------------------------------------------------------------------------------------------------------|
| GRADE 3 | Severe: Marked limitation in activity, some assistance usually required; medical intervention/therapy required. |
| GRADE 4 | Potentially Life-threatening: requires assessment in A&E or hospitalisation                                     |

Table 14. Severity grading criteria for local and systemic AEs.

### 9.11. Reporting Procedures for Serious AEs

In order to comply with current regulations on SAE reporting to regulatory authorities, the event will be documented accurately and notification deadlines respected. SAEs will be reported on the SAE forms to members of the study team immediately the Investigators become aware of their occurrence, as described in SOP OVC005 Safety Reporting for CTIMPs. Copies of all reports will be forwarded for review to the Chief Investigator (as the Sponsor's representative) within 24 hours of the Investigator being aware of the suspected SAE. The DSMB will be notified of SAEs that are deemed possibly, probably or definitely related to study interventions; the chair of DSMB will be notified immediately (within 24 hours) of the Sponsor being aware of their occurrence. SAEs will not normally be reported immediately to the ethical committee(s) unless there is a clinically important increase in occurrence rate, an unexpected outcome, or a new event that is likely to affect safety of trial participants, at the discretion of the Chief Investigator and/or DSMB. In addition to the expedited reporting above, the Investigator shall include all SAEs in the annual Development Safety Update Report (DSUR) report.

All AESIs not already reported as SAEs will be outlined in the DSMB reports.

### 9.12. Reporting Procedures for SUSARS

All SUSARs will be reported by the sponsor delegate to the relevant Competent Authority and to the REC and other parties as applicable. For fatal and life-threatening SUSARS, this will be done no later than 7 calendar days after the Sponsor or delegate is first aware of the reaction. Any additional relevant information will be reported within 8 calendar days of the initial report. All other SUSARs will be reported within 15 calendar days.

Principal Investigators will be informed of all SUSARs for the relevant IMP for all studies with the same Sponsor, whether or not the event occurred in the current trial.

### 9.13. Development Safety Update Report

A Development Safety Update Report (DSUR) will be prepared annually, within 60 days of the anniversary of the first approval date from the regulatory authority for each IMP. The DSUR will be submitted by the CI to the Competent Authority, Ethics Committee, HRA (where required), Host NHS Trust and Sponsor.

### 9.14. Procedures to be followed in the event of abnormal findings

Abnormal clinical findings from medical history or examination will be assessed as to their clinical significance throughout the trial. Decisions to exclude the participant from enrolling in the trial or to withdraw a participant from the trial will be at the discretion of the Investigator.

### **9.15. Interim Reviews**

The safety profile will be assessed on an on-going basis by the Investigators. The CI and relevant Investigators (as per the trial delegation log) will also review safety issues and SAEs as they arise.

An interim safety review of the first 7 days of safety data is planned after prime dose administration in all 12-17 year olds. 150 participants aged 12-17 years will have been recruited (of which 120 will be given a dose of the IMP). The data will be reviewed by the CI, relevant investigators and the chair of DSMB, as well as being provided to the MHRA, before proceeding with boosters in Groups 1 & 2. This safety review, if satisfactory, will allow age de-escalation. A sentinel group of 10 participants from the 6-11 year age groups (5 from each Group 3 & 4) will also be enrolled, given a prime dose and safety reviews by the CI, relevant investigators and the chair of DSMB and provided for review by the MHRA at D7 post prime in this sentinel group. If there is no safety signal from the D7 data in this sentinel group of 6-11 year olds, then recruitment of the remaining 111 participants in groups 3&4 will be allowed.

The DSMB will review safety data accumulated when the study is fully recruited. The DSMB will evaluate frequency of events, safety and efficacy data every 4-8 weeks and/or as required. The DSMB will make recommendations concerning the conduct, continuation or modification of the study.

### **9.16. Data Safety Monitoring Board**

A Data Safety Monitoring Board will be appointed to:

- a) periodically review and evaluate the accumulated study data for participant safety, study conduct, progress, and efficacy.
- b) make recommendations concerning the continuation, modification, or termination of the trial.

There will be a minimum of three appropriately qualified committee members of whom one will be the designated chair. The DSMB will operate in accordance with the trial specific charter, which will be established before recruitment starts.

The chair of the DSMB may be contacted for advice and independent review by the Investigator or trial Sponsor in the following situations:

- Following any SAE deemed to be possibly, probably or definitively related to a study intervention.
- Any other situation where the Investigator or trial Sponsor feels independent advice or review is important.

The DSMB will review SAEs deemed possibly, probably or definitively related to study interventions. The DSMB will be notified within 24 hours of the Investigators' being aware of their occurrence. The DSMB can recommend to place the study on hold if deemed necessary following a study intervention-related SAE.

### **9.17. Safety Group Holding Rules**

Safety holding rules have been developed considering the fact that this is the first time ChAdOx1 nCoV-19 is being administered to children.

Solicited AEs are those listed as foreseeable ARs in section 9.7 of the protocol, occurring within the first 7 days after vaccination (day of vaccination and six subsequent days). 'Unsolicited adverse events' are adverse events other than the foreseeable ARs occurring within the first 7 days, or any AEs occurring after the first 7 days after vaccination

### 9.17.1. Group holding rules

For safety reasons, vaccination will commence in the oldest age group, (150 participants aged 12-17 years, 120 of whom will receive the IMP). Group holding rules mentioned below will apply to all study Groups

- **Thrombosis**

Thrombosis of any kind including Cerebral Venous Sinus Thrombosis, Heparin-Induced Thrombocytopenia, major thrombosis with concurrent thrombocytopenia, stroke, pulmonary embolus or any other thromboembolism. If a thrombotic event occurs in any age group on any further vaccinations the trial will be stopped.

- **Solicited local adverse events:**

- If more than 25% of doses of the vaccine at a given time point (e.g. Day 0, Day 28, Day 112) in a study group are followed by the same Grade 3 solicited local adverse event beginning within 2 days after vaccination (day of vaccination and one subsequent day) and persisting at Grade 3 for >72 hrs

- **Solicited systemic adverse events:**

- If more than 25% of doses of the vaccine at a given time point (e.g. Day 0, Day 28, Day 112) in a study group are followed by the same Grade 3 solicited systemic adverse event beginning within 2 days after vaccination (day of vaccination and one subsequent day) and persisting at Grade 3 for >72 hrs

- **Unsolicited adverse events:**

- If more than 25% of doses of the vaccine at a given time point (e.g. Day 0, Day 28, D112) in a study group are followed by the same Grade 3 unsolicited adverse event beginning within 2 days after vaccination (day of vaccination and one subsequent day) and persisting at Grade 3 for >72 hrs

- **A serious adverse event considered possibly, probably or definitely related to vaccination occurs**

If a holding rule is activated, then further vaccinations in any group will not occur until a safety review by the DSMB, study sponsor and the chief investigator has been conducted and it is deemed appropriate to restart dosing. The Regulatory Authority will be informed and a request to restart dosing with pertinent data will be submitted as a substantial amendment. The safety review will consider:

- The relationship of the AE or SAE to the vaccine.
- The relationship of the AE or SAE to the vaccine dose, or other possible causes of the event.
- If appropriate, additional screening or laboratory testing for other participants to identify those who may develop similar symptoms and alterations to the current Participant Information Sheet (PIS) are discussed.
- New, relevant safety information from ongoing research programs on the various components of the vaccine.

The local ethics committee and vaccine manufacturers will also be notified if a holding rule is activated or released.

All vaccinated participants will be followed for safety until resolution or stabilisation (if determined to be chronic sequelae) of their AEs.

#### 9.17.2. Individual stopping rules

In addition to the above stated group holding rules, stopping rules for individual participants will apply (i.e., indications to withdraw individuals from further vaccinations). Study participants who present with at least one of the following stopping rules will be withdrawn from further vaccination in the study:

- **Local reactions:** Injection site ulceration, abscess or necrosis
- **Systemic solicited adverse events:**
  - the participant develops a Grade 3 systemic solicited AE considered possibly, probably or definitely related within 2 days after vaccination (day of vaccination and one subsequent day) and persisting continuously at Grade 3 for > 72hrs.
- **Unsolicited adverse events:**
  - the participant has a Grade 3 adverse event, considered possibly, probably or definitely related to vaccination, persisting continuously at Grade 3 for >72hrs.
  - the participant has a SAE considered possibly, probably or definitely related to vaccination.
  - the participant has an acute allergic reaction or anaphylactic shock following the administration of vaccine investigational product.

If a participant has an acute respiratory illness (moderate or severe illness with or without fever) or a fever (oral temperature greater than 37.8°C) at the scheduled time of administration of investigational product/control, the participant will not be enrolled and will be temporarily excluded from the study. They will be permitted to return in 10 days after recovery, in line with current self-isolation guidelines.

All vaccinated participants will be followed for safety until the end of their planned participation in the study or until resolution or stabilisation (if determined to be chronic sequelae) of their AEs, providing they consent to this.

In addition to these pre-defined criteria, the study can be put on hold upon advice of the DSMB, Chief Investigator, Study Sponsor, regulatory authority, Ethical Committee(s), for any single event or combination of multiple events which, in their professional opinion, jeopardise the safety of the participants or the reliability of the data.

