Participants or parent/guardian will complete diary cards for adverse event reporting of both local and systemic adverse effects and these will be reviewed at Day 7, prior to administering a booster dose to this cohort. Safety data will be reviewed by the CI, trial clinicians and DSMB.

Following the updated safety guidance from the JCVI on 8th April 2021, a decision was taken to halt recruitment into the study (at 261 participants) and for all remaining participants who were yet to receive a booster dose, to receive this at the 16-week interval. This would enable a further review by the MHRA/DSMB of updated safety data regarding administration of booster doses in adults, to inform a decision as to whether to continue with boosting children in this study.

Figure 2: Staggered enrolment strategy[figure not shown]

Participants will only be advised to take paracetamol for 24 hours from the time of vaccination if required for pain or other symptoms which should be recorded on their post-vaccination diary. They will not be advised to take prophylactic paracetamol.

Participants will be followed over the duration of the study to record adverse events and reported episodes of virologically confirmed symptomatic COVID-19 cases. Participants will be asked to inform the study team should they test positive in the community but no PCR testing will be done as part of this study. Participants will be provided with a phone number with which they can contact the study team clinician and the positive result together with symptoms will be entered electronically on the study database.

Mild, moderate and severe COVID-19 disease will be defined using clinical criteria, as outlined by the RCPCH [35]. These are likely to include, but are not limited to, oxygen saturation, need for oxygen therapy, respiratory rate and other vital signs, need for ventilatory support, chest imaging including CT scan, blood

test results and other relevant parameters. Should participants be admitted to hospital, participants will also be monitored for evidence of disease enhancement and evolution of PIMS-TS (via medical record review) during the study, as defined by RCPCH criteria [RCPCH, 2020].

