#### **9.7. Foreseeable Adverse Reactions:**

The foreseeable ARs following vaccination with ChAdOx1 nCoV-19 include injection site pain, tenderness, erythema, warmth, itch, swelling, fever/feverishness, chills, joint pain, muscle pain, fatigue, headache, malaise, nausea and vomiting.

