### 9.10. Reporting Procedures for All Adverse Events

All local and systemic AEs occurring in the 28 days following each vaccination observed by the Investigator or reported by the participant, whether or not attributed to study medication, will be recorded in electronic diaries or study database. All AEs that result in a participant's withdrawal from the study will be followed up until a satisfactory resolution occurs, or until a non-study related causality is assigned (if the participant consents to this). SAEs and Adverse Events of Special Interest (as outlined in Table 9) will be collected throughout the entire trial period.

The severity of clinical adverse events will be assessed according to scales based on FDA toxicity grading scales for healthy adolescents and children enrolled in preventive vaccine clinical trials. Severity grading criteria for temperature readings are given for adolescents. The normal ranges for a tympanic temperature in children aged 6-11 years is **35.8-38.0 C** (severity grading criteria not available).

Safety bloods will be assessed in accordance with normal ranges. Local sites will be responsible for following up any abnormal blood results the reference range which are of clinical concern. Severity grading scores are shown in Table 11, based on guidance from the Department of Aids (DAIDs) and OUH NHS Trust [37-38]

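### Individual stopping rules (Protocol 9.17.2): a related Grade 3 listed systemic reaction that starts on day 2 or 3, lasts over 72 h and ends before day 7 meets no mandatory rule, and no reason is given

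*Protocol*

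**What the plan says.** Meeting any one rule in Protocol 9.17.2 mandates withdrawal from further vaccination. Two of the rules concern prolonged Grade 3 events:

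- **Systemic solicited events:** "the participant develops a Grade 3 systemic solicited AE considered possibly, probably or definitely related within 2 days after vaccination", where the two days are the day of vaccination and the next day, and the event persists continuously at Grade 3 for more than 72 h.
- **Unsolicited events:** "the participant has a Grade 3 adverse event, considered possibly, probably or definitely related to vaccination, persisting continuously at Grade 3 for >72hrs". This rule has no onset limit.

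The opening of 9.17 defines the terms. Solicited events are the foreseeable reactions of section 9.7 "occurring within the first 7 days after vaccination (day of vaccination and six subsequent days"). The unsolicited class is defined as "adverse events other than the foreseeable ARs occurring within the first 7 days, or any AEs occurring after the first 7 days after vaccination". The systemic reactions listed in 9.7 are "fever/feverishness, chills, joint pain, muscle pain, fatigue, headache, malaise, nausea and vomiting".

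The other mandatory individual rules cover injection-site ulceration, abscess or necrosis, a related SAE, and acute allergic reaction or anaphylaxis. Section 6.3.3 adds anaphylaxis and pregnancy as absolute contraindications.

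**The concern.** Both Grade 3 rules ask for relatedness and more than 72 h continuously at Grade 3. Only the systemic solicited rule also asks that the event develop on day 0 or 1. A listed systemic reaction stays solicited through day 6, so from day 2 it is too late for the first rule and, because it is solicited, outside the second. A child could have a prolonged, related Grade 3 reaction and not be barred from the second dose. A child with the same reaction a day or two earlier, or from day 7, would be barred. This is a participant-safety rule in the first use of this vaccine under age 18. The primary safety analysis is not affected.

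**Working it through.** No figure in the protocol needs reproducing. The check sets the definitions against the rules and then finds the size of the gap.

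**Inputs.** Day 0 is the vaccination day, and hours run from the start of day 0. The solicited window is days 0-6, that is hours 0 to 168 (9.17). The systemic solicited rule covers days 0-1, hours 0 to 48 (9.17.2). Both rules need a duration above 72 h. Onset means the time at which Grade 3 is reached.

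**Step 1: the same event at different onsets.** Each event is related, non-serious, Grade 3 and longer than 72 h.

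| Event | Class under 9.17 | Mandatory rule met |
|---|---|---|
| Headache from day 1 | solicited | systemic solicited rule |
| Headache from day 2, lasting 80 h | solicited | none |
| Headache from day 8 | unsolicited | unsolicited rule |
| Unlisted event from day 2 | unsolicited | unsolicited rule |

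The 80 h headache starts between hours 48 and 72, so it ends between hours 128 and 152, before day 7 begins at hour 168.

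**Step 2: which onsets are clearly uncovered.** Let the onset hour be h. The event escapes the systemic rule if h ≥ 48. It lies wholly inside the solicited window if h + duration ≤ 168. With duration above 72 h, this needs h < 168 − 72 = 96. So 48 ≤ h < 96, which is days 2 and 3.

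**Step 3: width of the band.** The longest uncovered duration is 168 − h.

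- Start of day 2: 168 − 48 = 120 h.
- End of day 2, or start of day 3: 168 − 72 = 96 h.
- End of day 3: 168 − 96 = 72 h, where the band closes.

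A day 2 onset is therefore uncovered for durations above 72 h up to 96-120 h, depending on the hour. A day 3 onset is uncovered for durations above 72 h up to 72-96 h. Any event over 72 h that starts on days 4-6 runs into day 7 or later.

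**Step 4: which reactions.** Table 4 lists 10 systemic terms. For measured fever at ages 6-11, section 9.10 says "severity grading criteria not available", and Table 13 is titled for ages 13 and above. That leaves 10 − 1 = 9 terms that can be graded at every age in the trial.

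**Step 5: doses left for the rule to act on.** The Day 7 diary review falls 28 − 7 = 21 days before the earliest boost and 112 − 7 = 105 days before a D112 boost. The booster windows in Groups 2-4 close at day 140 after V1 (Tables 5b-5d). Suppose the last child was enrolled no later than about 8 April 2021, when recruitment stopped; the exact date is not given. Day 140 is then about 26 August 2021, before version 8.3 of 21 October 2021. What remains is mainly late second doses after unblinding (7.4.7).

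**The case against.** The two-day limit may be deliberate. All three Grade 3 group holding rules in 9.17.1 use it. The scheme also does not aim to stop dosing for every prolonged Grade 3 reaction: the local rule mandates withdrawal only for ulceration, abscess or necrosis. Safeguards exist as well. For diary cards, section 5 says "these will be reviewed at Day 7, prior to administering a booster dose to this cohort". The investigator may withdraw a child (6.3.5), and the study can be held for any single event (9.17.2).

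Part of this stands. The text is coherent once the defined terms are applied, and the safeguards lower the consequence. But they are discretionary and do not supply a mandatory rule. The group rules apply the limit to solicited and unsolicited events alike and do not require relatedness. The individual rules require relatedness and keep the limit for systemic solicited events only, without a stated reason.

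A reader might infer that the two rules contradict each other. The bullet "the participant has a SAE considered possibly, probably or definitely related to vaccination" sits under the unsolicited heading although a listed reaction can also be serious, which could suggest that the heading is not a filter. The Grade 3 bullet would then catch every onset day, and the two-day limit would do nothing. The documents do not support that as the main reading: 9.17 defines the heading's term just before it is used, and allergic reactions are not in the 9.7 list, so they fit under it. One over-broad bullet does not displace the definition.

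**Conclusion.** The gap holds as a minor point. With solicited and unsolicited as defined in 9.17, a related, non-serious Grade 3 listed systemic event that starts on day 2 or 3, lasts over 72 h and ends before day 7 meets no mandatory individual rule.

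A reader might extend the gap to all onsets on days 2-6. That follows only if an event is classed strictly by its onset. The unsolicited definition speaks of events occurring after the first 7 days, so an event still at Grade 3 on day 7 is arguably caught. Only the day 2-3 band is clear. Nor do the documents show that any child was boosted after such an event: they give no event rate, so no number affected can be stated.

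The conclusion assumes that the event is judged related and is not an SAE, and that developing within two days means reaching Grade 3 by the end of day 1. If an event that begins at a lower grade on day 1 and worsens later also counts, the band is smaller.

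**What to change.** In 9.17.2, delete the words that confine the individual systemic solicited rule to the day of vaccination and the day after. The rule then covers any related Grade 3 systemic solicited event lasting over 72 h with onset on days 0-6. Later onsets already fall under the unsolicited rule, so no onset day is left uncovered.

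Leave the local rule and the group holding rules in 9.17.1 unchanged. Do not instead widen the unsolicited bullet to any AE. That would also mandate withdrawal for prolonged Grade 3 local reactions and override the narrower local rule in the same section.

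The cost is one sentence and no new data collection. The downside is that a few more children might be withdrawn from the second dose.

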### 9.3. Serious Adverse Event (SAE)

An SAE is an AE that results in any of the following outcomes, whether or not considered related to the study intervention.

- Death
- Life-threatening event (i.e., the participant was, in the view of the Investigator, at immediate risk of death from the event that occurred). This does not include an AE that, if it occurred in a more severe form, might have caused death.
- Persistent or significant disability or incapacity (i.e., substantial disruption of one's ability to carry out normal life functions).

- Hospitalisation or prolongation of existing hospitalisation, regardless of length of stay, even if it is a precautionary measure for continued observation. Hospitalisation (including inpatient or outpatient hospitalisation for an elective procedure) for a pre-existing condition that has not worsened unexpectedly does not constitute a serious AE.
- An important medical event (that may not cause death, be life threatening, or require hospitalisation) that may, based upon appropriate medical judgment, jeopardise the participant and/or require medical or surgical intervention to prevent one of the outcomes listed above. Examples of such medical events include allergic reaction requiring intensive treatment in an emergency room or clinic, blood dyscrasias, or convulsions that do not result in inpatient hospitalisation.
- Congenital malformations or birth defects – structural, functional, genetic or behavioural anomalies, including metabolic disorders that occur during fetal development and can be diagnosed prenatally, at birth or later in life

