## CONFIDENTIAL

|         |  |      |                                                                    |             |              |                |         |
|---------|--|------|--------------------------------------------------------------------|-------------|--------------|----------------|---------|
| ALP     |  | IU/L | 6-10 yrs: 135-557
11-14yr (Boy) 92-549
11-14yr (Girl) 50-415 | 1-1.1 x ULN | 1.1 – 2x ULN | >2.5 – 5 x ULN | >5x ULN |
| Albumin |  | g/l  | 32-50                                                              | 28-32       | 28-32        | 25-27          | <25     |
| CRP     |  | mg/l | <10                                                                | <10         | 10-3-        | 31-100         | >100    |

Table 11: severity grading scales for abnormal blood results , ULN = upper limit of normal

Table 12. Severity grading criteria for local adverse events \*erythema  $\leq 2.5$ cm is an expected consequence of skin puncture and will therefore not be considered an adverse event

| Adverse Event                         | Grade | Intensity                                       |
|---------------------------------------|-------|-------------------------------------------------|
| Pain at injection site                | 1     | Pain that is easily tolerated                   |
|                                       | 2     | Pain that interferes with daily activity        |
|                                       | 3     | Pain that prevents daily activity               |
|                                       | 4     | A&E visit or hospitalization                    |
| Tenderness                            | 1     | Mild discomfort to touch                        |
|                                       | 2     | Discomfort with movement                        |
|                                       | 3     | Significant discomfort at rest                  |
|                                       | 4     | A&E visit or hospitalization                    |
| Erythema at injection site*           | 1     | 2.5 - 5 cm                                      |
|                                       | 2     | 5.1 - 10 cm                                     |
|                                       | 3     | >10 cm                                          |
|                                       | 4     | Necrosis or exfoliative dermatitis              |

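### The holding and stopping rules count only time at Grade 3, so a related event above Grade 2 for more than 72 hours can miss them when a Grade 4 period interrupts it

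*Protocol*

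**What the plan says.** Section 9.17.2 has two graded individual limbs. The systemic solicited limb withdraws a participant from further vaccination for a related Grade 3 event that starts on the day of vaccination or the next day, "persisting continuously at Grade 3 for > 72hrs". The unsolicited limb applies when "the participant has a Grade 3 adverse event, considered possibly, probably or definitely related to vaccination", with the same condition of continuous time at Grade 3.

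Section 9.17.1 has three percentage limbs (solicited local, solicited systemic, unsolicited). They hold vaccination when more than 25% of doses at a time point in a study group meet the condition. In the systemic limb, the doses counted are those that "are followed by the same Grade 3 solicited systemic adverse event beginning within 2 days after vaccination" (the day of vaccination and the next day) "and persisting at Grade 3 for >72 hrs". The word *continuously* does not appear in 9.17.1.

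The grading tables in 9.10 go one step higher:

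- Table 14, general scale, Grade 4: "Potentially Life-threatening: requires assessment in A&E or hospitalisation".
- Table 12, pain and tenderness, Grade 4: "A&E visit or hospitalization".
- Table 13, fever, Grade 4: an oral reading above 40°C, in a table headed for adolescents aged 13 and above.

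A related SAE triggers both sections separately. Section 9.3 does not make every Grade 4 event an SAE. The life-threatening criterion requires immediate risk of death and adds: "This does not include an AE that, if it occurred in a more severe form, might have caused death". The important-medical-event criterion covers events that may, "based upon appropriate medical judgment, jeopardise the participant" or require intervention to prevent a listed outcome.

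**The concern.** A rule that stops dosing for a persistent severe reaction should also stop it for a reaction that lasts as long and is worse for part of the time. As written, only time at exactly Grade 3 counts. A Grade 4 period breaks the continuous spell in 9.17.2, and under either section it removes hours from the time at Grade 3. A child who worsened to Grade 4 and was seen in A&E but not admitted could therefore miss a mandatory withdrawal that a child who stayed at Grade 3 would meet. The decision would then rest on investigator withdrawal (6.3.5) or on an advisory hold (last paragraph of 9.17.2).

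Two limits apply from the start. A Grade 4 event whose whole time above Grade 2 is 72 hours or less is outside this point, because neither the present nor the corrected wording would be met. Events already caught as a related SAE, thrombosis, acute allergic reaction or injection-site necrosis are also outside it.

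**Working it through.** The protocol gives no figure to reproduce on this point. The check applies the rule text to assumed grade courses, then counts thresholds and remaining doses.

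**1. Courses in hours (assumed).** A rule is met if the relevant time exceeds 72 h.

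| Course | Longest continuous Grade 3 | Total Grade 3 | Continuous Grade 3 or above |
|---|---|---|---|
| G3 80 h | 80 h, met | 80 h, met | 80 h, met |
| G3 40 h, G4 6 h, G3 40 h | 40 h, missed | 80 h, met | 86 h, met |
| G3 35 h, G4 10 h, G3 35 h | 35 h, missed | 70 h, missed | 80 h, met |
| G4 80 h | 0 h, missed | 0 h, missed | 80 h, met |

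The second column is the individual rule as written. The third is the group rule if it is read as cumulative time. The fourth is the corrected wording.

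**2. Courses in diary days (assumed).** Take a run of L days at Grade 3 or above with one Grade 4 day at position k, and count more than 72 hours as at least 4 consecutive Grade 3 days. The two Grade 3 spells last k − 1 and L − k days, so the individual rule is missed when max(k − 1, L − k) < 4.

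| L | Positions k that miss | Share |
|---|---|---|
| 4 | 1, 2, 3, 4 | 4 of 4 |
| 5 | 2, 3, 4 | 3 of 5 |
| 6 | 3, 4 | 2 of 6 |
| 7 | 4 | 1 of 7 |
| 8 | none | 0 of 8 |

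Example: malaise at Grade 3 on days 0 and 1, Grade 4 on day 2 (A&E, not admitted), Grade 3 on days 3 and 4. Here L = 5 and k = 3, the spells are 2 and 2 days, and the rule is missed. With no Grade 4 day the spell is 5 days and the rule is met. Under a cumulative reading of 9.17.1, L − 1 ≥ 4 is enough, so only the 4-day run is affected.

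**3. Group thresholds.** The smallest count above 25% of n is floor(0.25n) + 1.

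- ChAdOx1 doses only (Table 3 and Synopsis): 16 of 60 in Groups 1 and 2; 12 of 44 to 46 in Groups 3 and 4; 23 of 90 with Groups 3 and 4 pooled.
- All doses in the group: 19 of 75, 15 of 56, 14 of 55, 28 of 111.
- If 10% to 20% of 60 boosters are declined (assumed range; 6.3.6 expects some refusals): 14 of 54, 13 of 48.

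One lost event matters only at exactly these counts. For example, 15/60 = 25.0%, which is not more than 25%.

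**4. Doses still to come.** Recruitment stopped after the 8 April 2021 guidance (10.1), and the boost window runs to D140 (Tables 5b to 5d). Taking 8 April as the latest first dose, 8 April + 140 days = 26 August 2021. From then to version 8.3 on 21 October 2021 is 5 + 30 + 21 = 56 days. What can remain is delayed boosts after a positive PCR (6.3.3), second doses after unblinding (7.4.7) and an end-of-study course for controls (8.9). The last is at most (15 + 15 + 21) × 2 = 51 × 2 = 102 doses, and only if the vaccine is approved for the age group and the child is not eligible under the national programme. The protocol does not say whether 9.17 covers these doses.

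**The case against.** The strongest reply is that the example need not fail the rule. Table 14 defines Grade 4 by a care event and Grade 3 by the child's limitation and need for treatment. A child seen in A&E and sent home may still fit the Grade 3 description that day, and site staff would probably read the wording as at least Grade 3. That reading is possible, but the protocol nowhere states it, and a mandatory rule should not depend on it. The fever bands do exclude each other, though that table is headed for age 13 and above.

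Second, other safeguards overlap. Any admission is an SAE, a long related reaction seen in A&E may be judged an important medical event, and one related SAE both withdraws the child and holds all groups. This narrows the gap considerably. It does not close it, because the important-medical-event limb, investigator withdrawal and DSMB advice are all matters of judgement.

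Third, the protocol writes grade 3 or above for laboratory results, but Table 11 stops at Grade 3. That contrast does not show that Grade 4 was deliberately left out of 9.17. This is correct, and the point does not depend on it.

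Fourth, the individual rule acts mainly on reactions to the first dose, and first doses ended around April 2021. For late second doses, the reaction to the prime is already known. This stands and keeps the matter minor. The day-pattern counts also carry no event frequency; they show which courses are missed, not how often such courses occur.

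**Conclusion.** The concern holds as a minor error in the wording of a safety rule. Read literally, the five graded limbs let a worse course miss a rule that a milder course of the same length meets. This needs a related event (relatedness is not a condition in the percentage limbs), more than 72 hours above Grade 2, and a non-serious Grade 4 period that leaves no qualifying time at Grade 3.

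The effect falls mainly on the individual rule, where under the daily-grade assumptions runs of 4 to 7 days can be missed and runs of 8 days cannot. For the group rule it is negligible except at the exact threshold count. Few doses are likely to remain under version 8.3. No endpoint, estimate or sample size is affected. The conclusion rests on taking the grades as mutually exclusive, which the tables imply but do not state.

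**What to change.** In the three percentage limbs of 9.17.1 and the systemic and unsolicited graded limbs of 9.17.2, write *Grade 3 or above* for the event, and *at Grade 3 or above for more than 72 hours* for its persistence, keeping *continuously* where 9.17.2 has it. Leave the SAE, thrombosis, allergic-reaction and individual local-reaction limbs as they are.

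The cost is an edit to five limbs, repeated in the DSMB charter if the charter copies the rules. No new data are needed, because the diary cards already record timing and severity of solicited events (7.4.2.1). The only downside is that a trigger may be reached slightly sooner.
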